## Abstract

**Background::**

Infection caused by SARS-CoV-2 (severe acute respiratory syndrome coronavirus 2) exhibits a strong infectivity but less virulence compared to severe acute respiratory syndrome (SARS) and the Middle East respiratory syndrome (MERS). In terms of cardiovascular morbidity, susceptible population include elderly and patients with certain cardiovascular conditions. This infection has been associated with cardiac injury, cardiovascular complications and higher mortality.

**Objectives::**

The main objective of the CARDIO COVID 19-20 Registry is to determine the presence of cardiovascular comorbidities and cardiovascular complications in COVID-19 infected patients that required in-hospital treatment in different Latin American institutions.

**Methods::**

The CARDIO COVID 19-20 Registry is an observational, multicenter, ambispective, and hospital-based registry of patients with confirmed COVID-19 infection who required in-hospital treatment in Latin America. Enrollment of patients started on May 01, 2020 and was initially planned to last three months; based on the progression of pandemic in Latin America, enrollment was extended until December 2020, and could be extended once again based on the pandemic course in our continent at that moment.

**Conclusions::**

The CARDIO COVID 19-20 Registry will characterize the in-hospital population diagnosed with COVID-19 in Latin America in order to identify risk factors for worsening of cardiovascular comorbidities or for the appearance of cardiovascular complications during hospitalization and during the 30-day follow up period.

## Background

In December 2019, in Wuhan, China, various episodes of pneumonia caused by a new B-coronavirus (SARS-COV-2: Severe acute respiratory syndrome coronavirus 2) were identified and called Coronavirus Disease 2019 (COVID-19) by the World Health Organization (WHO) on February 11, 2020 [1]. This SARS-COV-2 has a zoonotic origin with a basic reproductive number or rate of contagion (R0) from 1.4 to 5.5 [2]. This high R0 led to a rapid expansion of COVID-19 cases in China, crossing borders to other continents, and leading to the declaration of the COVID-19 infection as a pandemic by the WHO on March 11, 2020 [3].

The main symptoms of this disease are fever (83-98%) and cough (76-82%). It is estimated that around 80% of cases are mild, 10%-15% are moderate, and up to 10% are severe and can present serious clinical manifestations, including cardiovascular and respiratory complications. Currently, several platforms record the number of cases by COVID-19 in a real and simultaneous way, such as Johns Hopkins University, USA. On March 27, 2020, this platform reported 558,502 confirmed cases, 25,251 deaths and 127,615 people recovered worldwide [1,4,5,6].

COVID-19 infection represented a health emergency in Europe, especially in Italy and Spain, and currently in the United States and Latin America. This health emergency has led different countries to implement rigorous political, economic, and social measures to prevent or delay the expansion of the SARS-COV-2 infection [7].

Pneumonia caused by SARS-CoV-2 exhibits strong infectivity, but less virulence compared to severe acute respiratory syndrome (SARS) and the Middle East respiratory syndrome (MERS). In terms of morbidity and mortality, susceptible population include elderly and patients with certain cardiovascular conditions. So far, treatments combined with powerful antiviral drugs, such as remdesivir, chloroquine, or lopinavir/ritonavir have shown confounding results. Based on that, more clinical trials are currently undergoing in order to determine the most specific transmission mechanisms, virulence, and pharmacological response [1].

Cardiovascular complications of influenza infection include myocarditis, acute myocardial infarction, and exacerbation of heart failure, well known during previous historical epidemics. Similarly, outbreaks of coronavirus have been associated with a significant burden of cardiovascular comorbidities and complications. Furthermore, the severity of the primary respiratory syndrome and the risk of adverse outcomes increases in patients with cardiovascular disease. Hypotension, tachycardia, bradycardia, arrhythmias, or even sudden death are common in patients with SARS [8].

In a retrospective multicenter cohort study of adult patients hospitalized with a confirmed diagnosis of COVID-19, of whom 137 were discharged and 54 died in hospital, high blood pressure was the most common comorbidity followed by diabetes mellitus and coronary heart disease. The multivariate regression showed higher probabilities of hospital death associated with older age, higher SOFA score (Sequential Organ Failure Evaluation Score) and D-dimer higher than 1 μg/ml on admission. The longest duration of virus clearance observed in survivors was 37 days [9].

The increased morbidity and mortality of COVID-19 in patients with high blood pressure have been observed in epidemiological studies in China. The association between Angiotensin-Converting Enzyme-2 (ACE-2) and SARS-CoV-2 infection have been described previously; ACE-2 acts as a co-receptor for the entrance of SARS-CoV-2 into the bloodstream. Based on this preliminary information, a concern related to the use of Angiotensin-Converting Enzyme inhibitors (ACEi) and Angiotensin-Receptor Blockers (ARB) in this population increased because the risk of higher severity and mortality in COVID-19. Observational studies showed no clinical evidence of cardiovascular adverse outcomes with the use of these drugs and a recent randomized clinical trial confirmed this finding [10,11]. The Council of Hypertension of the European Society of Cardiology and other international societies published different statements clarifying this topic and recommended continuing cardiovascular treatment with these drugs [12,13].

## Methods and Design

### Study population

The study population will include hospitalized patients with confirmed COVID-19 infection, with or without previous cardiovascular comorbidities.

### Inclusion criteria

Patients older than 18 years with confirmed diagnosis of COVID-19 according to guidelines given by the World Health Organization and according to each institutional and/or local guideline, andwho requires in-hospital management for more than 24 hours related to COVID-19, orwho dies during the first 24 hours after hospital admission

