## Data Analysis

This study will obtain different data that will be used to calculate lethality and frequency of complications during hospitalization and follow-up, and to characterize the overall in-hospital population. Hospital fatality (number of deaths attributed by COVID-19/number of patients diagnosed with COVID-19), incidence of in-hospital cardiovascular complications (number of new complications due to specific cardiovascular cause in COVID-19 patients/number of patients diagnosed with COVID-19), and survival analysis (the probability of death by time interval can be calculated) will be determined by the Kaplan Meier method and presented by a graph.

Characterization of the in-hospital population will be carried out through an univariate analysis to determine the behavior of numerical variables, the normality of the variables will be determined with a Shapiro Wilk test, those with a p > 0.05 will be considered with normal distribution and will be presented with averages and standard deviation; those with a non-normal distribution will be presented with median and interquartile ranges. The categorical variables will be presented as proportions.

The quantitative variables will be compared, in case of a normal distribution, by the Student’s t-test or ANOVA. If the normality criterion is not met, a non-parametric test will be used. For the comparison of categorical variables, Fisher’s exact test or X^2^ test will be used. For the analysis of patient outcomes with COVID-19 based on demographic, laboratory values, and/or clinical variables, the relation of these variables will be evaluated with a multivariate logistic or linear regression models, depending on the outcome variable to evaluate.

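### Entry to the registry depends on the 24-hour outcome: early deaths are kept, short-stay survivors are not, so fatality per hospitalized case is biased upward

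*Protocol article*

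**What the plan says.** Three places in the protocol article bear on this.

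- **Inclusion criteria.** Both routes require the same starting point: "Patients older than 18 years with confirmed diagnosis of COVID-19". Beyond that, a patient enters who "requires in-hospital management for more than 24 hours related to COVID-19, orwho dies during the first 24 hours after hospital admission". The first route is the longer stay and the second is the early death. The second route, as printed, has no condition that the admission or the death be related to COVID-19.
- **Study population.** "The study population will include hospitalized patients with confirmed COVID-19 infection, with or without previous cardiovascular comorbidities". No minimum stay and no condition on survival appear here.
- **Data Analysis.** Hospital fatality is "number of deaths attributed by COVID-19/number of patients diagnosed with COVID-19". The same section plans a Kaplan-Meier survival analysis, from which "the probability of death by time interval can be calculated", with no restriction on cause of death. It also plans regression models for patient outcomes. Table 1 records length of stay and whether the patient was alive or dead at discharge.

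Nothing in the article reconciles the entry rule with the broader population or with the fatality denominator.

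**The concern.** Two patients who look the same on arrival can differ in eligibility only because one dies and the other goes home within a day. That is selection on the outcome. The registry is ambispective (Study design), so the 24-hour outcome may already be known when a patient is entered.

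Two results are at stake. Fatality is the first rate defined in Data Analysis, and it is described as if it applied to everyone diagnosed. The Introduction also aims to relate baseline characteristics, cardiovascular comorbidities and treatments to worse outcomes. A confirmed patient admitted for a primarily cardiac reason enters if death comes within 24 hours, but may not enter if alive at that point. An association between acute cardiovascular presentation and death could be distorted by that rule alone, and enrolling more patients would not remove the distortion.

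**Working it through.** The article states no expected fatality, sample size or excluded share, so there is no planned figure to reproduce. The entry rule, the population and the fatality definition come from the article. Every numerical input below is an assumption, used to show direction and scale.

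**Step 1. Who enters, among confirmed patients**

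| Status at 24 h | Care related to COVID-19 | Care not related |
|---|---|---|
| Dead | enters | enters |
| Discharged alive | excluded | excluded |
| Alive in hospital | enters | excluded |

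Every early death enters. Every exclusion falls on someone alive at 24 hours.

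**Step 2. Attributed fatality.** Let D be COVID-19-attributed in-hospital deaths, N all hospitalized confirmed cases, and E those excluded. Early attributed deaths enter by the second route. Later ones enter by the first, provided that such a death was preceded by COVID-19-related care. E therefore contains none of D, and

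D/(N-E) ≥ D/N, strictly greater if anyone is excluded.

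Counting only short-stay survivors, with s = E/N and true fatality F = D/N, registry fatality is F/(1-s) and the relative excess is 1/(1-s)-1:

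| s (assumed) | Relative excess | F = 10% | F = 20% | F = 30% |
|---|---|---|---|---|
| 2% | 2.0% | 10.20% | 20.41% | 30.61% |
| 5% | 5.3% | 10.53% | 21.05% | 31.58% |
| 10% | 11.1% | 11.11% | 22.22% | 33.33% |

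**Step 3. Early deaths from other causes.** Take 1000 COVID-19-related admissions, F = 20%, s = 0, and add x other-cause deaths within 24 hours that enter by the second route.

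- Attributed fatality, 200/(1000+x): 19.90% at x = 5 and 19.80% at x = 10. It falls, because these deaths reach only the denominator.
- All-cause fatality, (200+x)/(1000+x): 20.40% at x = 5 and 20.79% at x = 10. It rises.

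**Step 4. All-cause fatality against all hospitalized confirmed cases.** Add 100 admissions not related to COVID-19, of which 5 die within 24 hours. The registry gives 205/1005 = 20.40%. The full population gives (205+y)/1100, where y is the number of later deaths among the other 95. With y = 0 this is 18.64%, so the registry is too high. The two agree at y = 205 × 95/1005 = 19.4. With 20 or more later deaths, the registry is too low. The sign depends on y, which the article does not give.

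**Step 5. Would dropping early deaths repair it?** Let e be the share of admissions dying early. Requiring more than 24 hours of everyone gives (F-e)/(1-s-e). With F = 20% and s = 5%, that is 0.18/0.93 = 19.35% at e = 2% and 0.15/0.90 = 16.67% at e = 5%. The bias now runs downward. Keeping early deaths is sound; the defect is that the two routes differ.

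**The case against.** The best defence is that the benchmark is too wide. The Objectives and Study design speak of patients who required in-hospital treatment. A stay above 24 hours is a reasonable working definition of that need, and adding early deaths stops the most severe cases from being lost through the time threshold. On this view the Study population sentence is a summary that the Inclusion criteria make specific. This is a fair reason for having both routes. It does not explain why only one carries a relatedness condition, and it does not make patients diagnosed with COVID-19 the right name for the denominator.

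A reader might infer that early deaths from any cause inflate the registry's hospital fatality. The documents do not support that. The numerator is limited to deaths attributed to COVID-19, so unrelated early deaths slightly lower the ratio (step 3), and adding a relatedness condition to the death route would slightly raise it. The upward bias in this measure comes from the missing survivors.

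It also stands that fatality is not the main objective, which concerns cardiovascular comorbidities and complications. Enrolling short-stay survivors at sites across 20 countries, after enrollment has begun, would not be a small change.

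**Conclusion.** The point holds in a limited form. Eligibility depends on the 24-hour outcome, and the relatedness condition applies to one route only. Relative to all hospitalized confirmed cases, COVID-19-attributed fatality is biased upward whenever anyone is excluded. This rests on the rule as printed and on later attributed deaths having followed COVID-19-related care. The relative excess of 2.0% to 11.1% follows wholly from assuming that s is 2% to 10%. If few patients leave alive within a day, it is small.

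For all-cause measures and models of death, unrelated early deaths enter without their matching survivors and can distort associations with acute cardiovascular presentation. One might go further and say that this inflates all-cause mortality, or that the bias is larger in cardiovascular emergencies. Neither is shown: patients excluded as alive at 24 hours with unrelated stays may die later, and step 4 shows that the sign can reverse.

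The plan should be corrected on this point. The remedy is cheap, and the defect does not undermine the registry's descriptive purpose.

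**What to change.** 1. **Keep early deaths and align the routes.** Apply the same COVID-19-relatedness condition to deaths within 24 hours as to longer stays. Judge it from the reason for admission, not the cause of death; otherwise selection on the outcome returns in another form. Table 1 in the article names no reason-for-admission item, so for patients already enrolled this may need a short look back at the records.
2. **Name the denominator.** State that fatality is per enrolled patient under the inclusion criteria, not per patient diagnosed or hospitalized with COVID-19. This discloses the missing short-stay survivors but does not recover them. Enrolling them is not needed.
3. **Add a 24-hour landmark analysis.** Report Kaplan-Meier estimates and mortality models also for patients alive and in hospital at 24 hours, with time counted from that point. Entry to this set no longer depends on a death before the landmark. Length of stay and vital status are already collected.

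Items 2 and 3 cost wording and one additional analysis; item 1 is a small amendment. The landmark analysis omits the earliest deaths and answers a question conditional on reaching 24 hours, so it belongs beside the main estimate and does not replace it.

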### Informed Consent

Informed consent is not required because this is an observational study. If any institution requires informed consent, a form that was validated by the CIC and the Ethics Committee of the FVL is available and can be used.

### Study design

The CARDIO COVID 19-20 Registry is an observational, multicenter, ambispective, and hospital-based registry that includes patients with confirmed COVID-19 that require in-hospital treatment in Latin American medical institutions. Enrollment of patients started on May 01, 2020 and was initially planned to last three months; however, based on the progression of the pandemic in Latin America, enrollment was extended until December 2020, and could be extended once again based on the pandemic course in this continent at that time.

The Scientific Committee is composed by members of the Council of Heart Failure and Pulmonary Hypertension (CIFACAH) and the Interamerican Society of Cardiology (IASC). It has the approval of the Clinical Research Center (CIC) and the Ethics Committee of the Fundación Valle del Lili (FVL) and the Scientific and Academic approval of IASC.

### Site selection

The Steering Committee of the Registry designated a national coordinator in the 20 Latin American countries that will be included; from Central America: Mexico, Guatemala, Honduras, El Salvador, Nicaragua, Costa Rica, Panama, Dominican Republic, Cuba and Puerto Rico; and from South America: Colombia, Venezuela, Brazil, Ecuador, Peru, Bolivia, Uruguay, Paraguay, Chile and Argentina. (Figure 1) The IASC and CIFACAH are working with those designated national coordinators and the presidents of the national cardiovascular societies or associations of these countries (who must be affiliated to the IASC) to identify potential researchers (e.g., internal medicine specialists, cardiologists or intensivists) that will be contacted and invited to participate in this project. Those identified professionals and institutions must complete a digital form submitting data to the research team (principal investigator and sub investigator).

**Figure 1 F1:**
[figure not shown]
Participant countries in Central and South America.

## Data Collection

Information (variables) will be collected in the electronic database system RED Cap (Research Electronic Data Capture: https://www.project-redcap.org/). This database system will include 277 variables that will be distributed in 15 different files (Table 1).

**Table 1 T1:** Information to be collected.

Information	Variables

Demographics	*Age, gender, and other variables that will allow this population to be characterized*
Comorbidities	*Mainly cardiovascular pathologies including hypertension, coronary artery disease, heart failure and dyslipidemia, among others. Other high-risk comorbidities like cancer, immunosuppressive conditions, obesity, diabetes mellitus, COPD and renal failure will be included*.
Previous cardiovascular treatment	*ARB/ACEi/ARNI, and other drugs like beta blockers, diuretics, antiplatelet and anticoagulant agents*
Symptoms at admission	*Includes the most frequently reported (fever, cough, chest pain, and fatigue) and other less frequent variables (dysphagia, loss of taste or smell, myalgias, diarrhea…)*
Clinical findings at admission	*Basic hemodynamic and metric evaluation*
Cardiovascular complications during hospitalization	*Myocarditis, arrhythmias, heart failure, coronary artery events, venous or arterial thrombosis*
Laboratory test at admission	*Complete blood count, kidney and liver function tests, cardiovascular biomarkers and inflammatory biomarkers*
Electrocardiography	*Rhythm, QRS complex, bundle, branch block, corrected QT interval*
Chest X-Ray	*Pulmonary infiltrates, cardiomegaly, lung congestion, pleural effusion*
Echocardiography	*RV systolic function, pericardial effusion, cardiac tamponade, valvular function, vena cava dilatation, measurement of LV size and LV global systolic function*
Cardiovascular procedures performed during hospitalization	*Central catheters, use of inotropes, vasopressors or vasodilators, mechanical ventilation, ventricular assist devices (IABP, ECMO)*
COVID-19 treatment during hospitalization	*Steroids, antivirals, anti-inflammatory, anticoagulant or any other used treatment*
Laboratory tests at discharge	*Complete blood count, kidney and liver function tests, cardiovascular biomarkers and inflammatory biomarkers*
Outcomes during hospitalization and at discharge	*Length of stay, condition at discharge (alive or dead)*
Outcomes 30 days after discharge	*Rehospitalization, condition at follow up (alive or dead)*

COPD: Chronic Obstructive Pulmonary Disease; ARB: Angiotensin-Receptor Blockers; ACEi: Angiotensin-Converting Enzyme Inhibitors; ARNI: Angiotensin Receptor Neprilysin Inhibitor; RV: Right Ventricle; LV: Left Ventricle; IABP: Intra-Aortic Balloon Pump; ECMO: Extracorporeal Membrane Oxygenation.

Each institution will be coded, as well as the identity of every enrolled patient. Weekly quality control will be carried out in each participant center in order to verify the integrity of the data collected and will be informed about discrepancies found in the registered data.

## Data Analysis

This study will obtain different data that will be used to calculate lethality and frequency of complications during hospitalization and follow-up, and to characterize the overall in-hospital population. Hospital fatality (number of deaths attributed by COVID-19/number of patients diagnosed with COVID-19), incidence of in-hospital cardiovascular complications (number of new complications due to specific cardiovascular cause in COVID-19 patients/number of patients diagnosed with COVID-19), and survival analysis (the probability of death by time interval can be calculated) will be determined by the Kaplan Meier method and presented by a graph.

Characterization of the in-hospital population will be carried out through an univariate analysis to determine the behavior of numerical variables, the normality of the variables will be determined with a Shapiro Wilk test, those with a p > 0.05 will be considered with normal distribution and will be presented with averages and standard deviation; those with a non-normal distribution will be presented with median and interquartile ranges. The categorical variables will be presented as proportions.

The quantitative variables will be compared, in case of a normal distribution, by the Student’s t-test or ANOVA. If the normality criterion is not met, a non-parametric test will be used. For the comparison of categorical variables, Fisher’s exact test or X^2^ test will be used. For the analysis of patient outcomes with COVID-19 based on demographic, laboratory values, and/or clinical variables, the relation of these variables will be evaluated with a multivariate logistic or linear regression models, depending on the outcome variable to evaluate.

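### Student's t-test and ANOVA are conditioned on normality alone; Welch's versions would remove an unneeded equal-variance assumption in this non-randomised registry (minor)

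*Protocol article*

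**What the plan says.** All of the relevant text is in the Data Analysis section of the protocol article. Normality is assessed first: "the normality of the variables will be determined with a Shapiro Wilk test", and "those with a p > 0.05 will be considered with normal distribution". The choice of test follows from that result. Variables are compared "in case of a normal distribution, by the Student’s t-test or ANOVA", and otherwise: "If the normality criterion is not met, a non-parametric test will be used". The section mentions neither equality of variances nor an unequal-variance version of either test. It does not say which groups will be compared, and it sets no significance level for the comparisons. The only 0.05 in the article is the Shapiro-Wilk cut-off.

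The Study design section describes an "observational, multicenter, ambispective, and hospital-based registry", so no allocation mechanism balances the groups.

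**The concern.** Student's t-test and classical ANOVA rest on two distributional conditions: normality, and a common variance across groups. The article conditions on the first and is silent on the second. The pooled standard error is robust to unequal variances when groups are of equal size, but not otherwise. If the smaller group is the more variable, the pooled standard error is too small and false positives increase. If it is the less variable, the standard error is too large and real differences are missed.

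Groups in a registry form themselves. Natural comparisons, given the article's aims, are died versus survived and with versus without a cardiovascular complication. These groupings are inferred, because the Data Analysis section does not list them. Such groups need not be similar in size or in spread. At stake is whether the p-values for mean differences can be taken at face value for the variables that reach this branch.

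**Working it through.** The plan states no error rate, sample size or SD, so there is no figure to reproduce. The check asks how far Student's test departs from a nominal level under stated assumptions.

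**Inputs**
- Level: 5% two-sided. Assumed.
- Share f of patients in the smaller group: the Background describes a hospital cohort "of whom 137 were discharged and 54 died in hospital", so 54/(137 + 54) = 54/191 = 28%. This is outside data, used only as a proxy. A share of 20% is added as a further assumption. The worldwide counts in the Background are of confirmed cases, not hospitalised patients, and are not used.
- SD ratio r (smaller group over larger group): the article gives none. Assumed range 0.67 to 2.

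**Formula** (large samples, SD of the larger group set to 1, variances multiplied by the total sample size)
- True variance of the mean difference: V_true = r²/f + 1/(1 − f)
- Variance that Student's test uses: V_pooled = (f·r² + 1 − f) / (f(1 − f))
- Actual type I error: 2·[1 − Φ(1.96·√(V_pooled/V_true))]

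**Worked case**, f = 0.28 and r = 1.5
- V_true = 2.25/0.28 + 1/0.72 = 8.036 + 1.389 = 9.425
- V_pooled = (0.63 + 0.72)/0.2016 = 6.696
- √(6.696/9.425) = 0.843, and 1.96 × 0.843 = 1.652
- Type I error = 9.9%

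**Results**

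| Smaller group | r = 0.67 | r = 1 | r = 1.25 | r = 1.5 | r = 2 |
|---|---|---|---|---|---|
| 28% | 2.0% | 5.0% | 7.5% | 9.9% | 13.5% |
| 20% | 1.3% | 5.0% | 8.6% | 12.1% | 17.9% |
| 50% | 5.0% | 5.0% | 5.0% | 5.0% | 5.0% |

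The last row and the r = 1 column show that the departure needs unequal sizes and unequal SDs together.

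**Simulation check.** With normal groups, 1,000 patients and a 20% minority, Student's test rejected in 1.3%, 11.5% and 17.3% of null datasets at r = 0.67, 1.5 and 2, in line with the formula. Across minorities of 10% and 20% and r from 0.5 to 2, Welch's test stayed between 4.5% and 5.4%. Classical ANOVA behaves similarly: with groups of 700, 200 and 100 and the two smaller groups at r = 1.5, it rejected in 13.3%.

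**Does the normality step help?** The article does not say whether Shapiro-Wilk is run within groups or on the whole variable, so both were simulated with normal groups.
- *Within groups:* about 90% of datasets pass whatever the SD ratio. Among those passing, Student's error is essentially unchanged (11% to 12% for a 20% minority at r = 1.5).
- *Pooled variable, large ratio:* for a 20% minority at r = 1.5, 80% pass with 200 patients, 44% with 1,000 and 6% with 3,000. At r = 2, 29% pass with 200 and none with 1,000.
- *Pooled variable, modest ratio:* for a 20% minority at r = 1.25, 92%, 92%, 90% and 89% pass with 150, 300, 500 and 1,000 patients. Among those passing, Student's error is 8.2% to 8.9%, against 4.8% to 6.1% for Welch's test.

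**The case against.** The strongest reply has four parts.

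*Nothing in the article establishes the conditions.* It names no groups and gives no group sizes or SDs. A reader might infer that the groups will be very unequal, or that a stated error rate is breached by a factor of two to three. The documents support neither: no level is set for these comparisons, and the nearest proxy for group size is 28% from another cohort. This stands, and every figure here is therefore conditional.

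*The normality step may itself remove the bad cases.* A reader might infer that it gives no protection at all. That is right for within-group testing. If the pooled variable is tested, however, most large SD ratios fail in samples of a few thousand and never reach Student's test. Many real registry variables will also fail for ordinary skewness. This stands in part. It narrows the reach of the problem, but modest ratios still pass, and Student's test is still off level among those that do.

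*The comparisons are secondary.* They are unadjusted, and the same section assigns the relation of patient variables to outcomes to multivariable regression. A reader might also infer that confidence intervals for mean differences would be wrong, but the article plans none. This stands and limits the severity.

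*Variance handling is a detail for a fuller plan, which is not shown.* This does not dispose of the point. The article names a specific test and attaches a specific condition, so the comment concerns a choice that was made, not an omission.

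One further limit is that changing this branch does not touch the unnamed non-parametric test. On the same simulated data Mann-Whitney was also off nominal, at about 7% to 11% for ratios above 1 and 0.6% to 3.5% below 1.

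**Conclusion.** The point holds as a minor, conditional improvement. The article selects equal-variance tests on a condition that does not include equal variances, in a design that gives no reason to expect them. If groups differ in both size and spread, p-values from this branch can be moderately too small or too large, by the amounts tabulated above. Those amounts rest on an assumed 5% level, assumed SD ratios, and a group share that is either borrowed from an outside cohort (28%) or assumed (20%). If sizes or SDs are equal, there is no problem. The hospital fatality, complication-incidence and Kaplan-Meier results do not use these tests and are unaffected.

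**What to change.** In the Data Analysis section, replace Student's t-test or ANOVA with Welch's t-test for two groups and Welch's ANOVA for more than two. This takes one sentence and a software option. The downside is a loss of power when variances happen to be equal, which is negligible at registry sample sizes. No other analysis needs to change on account of this point.
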